#### Secondary outcome measures

Secondary outcome measures include patient activation, medication adherence, health-related quality of life, and cost effectiveness. In regard to cost-effectiveness, to understand the financial burden associated with study participation, we will conduct a brief survey with participants at the completion of the study about costs they have incurred. These data will be combined with additional measures (e.g., ED and hospital recidivism) compiled by review of hospital records to derive estimates of the cost effectiveness of a kiosk-based approach to ED discharge, from a public health perspective.

Patient activation will be measured by The Patient Activation Measure (PAM) [40], a unidimensional thirteen item scale assessing patient knowledge, skill and confidence in self-management behaviors. Patients rate how strongly they agree/disagree with each item. Besides obtaining an activation score, responses can be used to stage individuals along an activation continuum: (1) believes active role is important, (2) confidence and knowledge to take action, (3) taking action, and (4) staying the course under stress. All participants will use the kiosk to complete the tool at baseline, 90, and 180 days post enrollment.

Medication adherence using the Morisky Medication Adherence Scale (MMAS) will be used to assess self-management behavior. The eight item MMAS, a self-report assessment tool shown to have a statistical association with antihypertensive medication refill rates, will be completed at 30, 90 and 180 days [41], also through the kiosk. Clinical research staff will conduct pill counts as part of medication monitoring at each follow-up appointment. Using fixed denominators based on a known quantity of medication dispensed at the prior evaluation, drug-specific and overall measures of antihypertensive therapeutic intensity will be derived.

A cost-effectiveness approach will be used to compare health outcomes (BP control) between the control and intervention groups [42]. The analysis will assume the objective of BP control is desirable even if the benefits have not yet been evaluated in monetary terms. The cost-effectiveness approach can be a useful step towards undertaking a cost-benefit study [43]. Because the study ultimately seeks to determine if an enhanced discharge can reduce ED return visits, this analysis will focus on the cost-saving comparison between groups as it relates to ED usage solely as related to hypertension. Clinical staff and hospital costs incurred at the ED visit as well as costs associated with follow-up (facility and staffing costs) will be measured. Participants will complete a brief survey about time and money costs they incurred from participating in the intervention study [44]. Additional information such as the number and reasons for return visits to the ED will be obtained from medical records.

### Statistical analysis

The OnCore Clinical Trial Data Management System, which is internet accessible and HIPAA compliant, will be used for protocol management & data entry. Primary analyses will be conducted using IBM SPSS (v. 20). Initial analyses will consist of descriptive statistics including univariate and bivariate frequency distributions. Differences in baseline socio-demographic and medical variables between the two groups will be used as covariates if appropriate statistical assumptions are met. Tests of the hypotheses will use the intent to treat analysis and all available outcome data.

To assess if the intervention improves blood pressure control over standard discharge practices, differences between groups will be assessed using blood pressure as a continuous variable (i.e., changes in systolic/diastolic readings) and as a dichotomous variable (i.e., number of patients with controlled blood pressure.

A generalized linear mixed model analysis will be used to test differences between groups over time, using continuous blood pressure measures. Both groups are expected to show decreases in blood pressure over time but with greater decreases for the intervention group. Thus, for the continuous blood pressure measures, the major effect of interest will be the linear group x time interaction. We assume that decreases in blood pressure over the time periods will be roughly linear, although a quadratic time effect may also occur. Based on a standard deviation of 12 mmHg for systolic blood pressure, a clinically relevant decrease of 6 mmHg systolic blood pressure (i.e., d = .5), and a one-sided alpha of .05, the study will have adequate power (.80) with 50 subjects in each group. This is a somewhat conservative estimate which does not take into account repeated measures, blocking, or possible covariate adjustments, all of which would tend to increase power.

Group differences in decreased percentages of those with uncontrolled blood pressure will be compared at each time point. Percentages will be compared using the arc sine transformation. For power assessment, we assume a medium effect size of h = .5 [45], where h is the difference between arc sine values for the population proportions of the two groups. Illustrative pairs of proportions for h = .5 are 60–35, 65–40, 69–45, and 79–50. For these effect sizes, *n* = 50, and a one-sided alpha of .05, power would be .80. General linear models will be used to test the full range of assessment periods.

In addition to assessing the primary outcome, the project will assess two secondary hypotheses related to patient activation. Analysis of covariance using the baseline activation score as covariate will be conducted to test for significant differences in patient activation scores between groups at the 180 day assessment. Pearson correlations and subsequent multiple regression analyses will test the association between patient activation scores and engaging in self-monitoring of blood pressure, medication adherence scores, demographics, and number of subsequent emergency department and primary care visits. Logistic regressions will explore differences in participant study completion and in obtaining BP control.

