## Methods

### Study design and aims

Achieving Blood Pressure Control Through Enhanced Discharge (AchieveBP) is a behavioral patient education intervention. It is a longitudinal, randomized controlled study in which ED patients with uncontrolled hypertension receive either an educationally enhanced or a standard discharge procedure. Study outcomes are assessed at baseline, 30, 90, and 180 days post ED discharge.

The design and conduct of the study adheres to the Consolidated Standards of Reporting (CONSORT) guidelines [37]. The study was approved by the Wayne State University Medical Institutional Review Board (M1, IRB#050213M1F) on 23 July 2013, and is registered with ClinicalTrials.gov (#NCT02069015). The study is administered through the Department of Family Medicine & Public Health Sciences in partnership with the Department of Emergency Medicine at the Wayne State University School of Medicine. Results of this study will be disseminated via scientific forums, including peer-reviewed publication and presentations at national and international conferences.

The primary aim of the study is to determine if integrating kiosk-based patient education via health information technology into the ED discharge process, coupled with additional educational sessions outside the ED will improve BP control compared to the usual discharge process. The secondary aim is to explore the relationship between patient activation, self-management behaviors (e.g., BP medication adherence), and health care utilization (i.e., return hospital emergency department visits). Cost effectiveness of the intervention will be assessed as well.

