**Fig. 2 Fig2:**
[figure not shown]
Study flow chart

Given the differential definition for blood pressure control, a stratified random sampling procedure will be used, based on self-reported diabetic diagnosis. A block randomization schedule will be developed using a separate computer-generated random number table for diabetic and non-diabetics. Once diabetic status is determined, research staff will use the appropriate table to assign the participant to one of two study arms:

• Standard discharge (Attention control group) who will receive the ED’s usual discharge instructions for follow-up care. These materials typically include an accounting of major procedures and tests performed during the emergency department visit, principal diagnosis at discharge/chief complaint, patient instruction, follow-up care and medication/prescription.

• Intervention group, who, in addition to receiving the standard printed materials, will also receive a hypertension curriculum delivered via a touch screen kiosk with attached blood pressure monitor.

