### Study outcomes

#### Primary outcome measure

The primary health outcome measure is short-term patient BP control. Blood pressure will be assessed using the BpTRU device (Smiths Medical PM, Inc; Waukesha, WI) which provides up to six automated measurements with initiation of the process by the patient rather than a health care provider. Blood pressure will be taken using this device at all assessment periods. Both the difference in the actual BP readings and the proportion of persons in each group achieving BP control at 180 days will be used to assess study outcomes. BP control is defined as at or below 140/90 for non-diabetics and at or below 130/80 for diabetics.

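### Covariates are to be picked from observed baseline differences, a rule that tends to pass over the diabetes stratum, and the comparison of 180-day BP control names no adjustment for it

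*Protocol article*

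**What the plan says.** The Statistical analysis section states how covariates will be chosen: "Differences in baseline socio-demographic and medical variables between the two groups will be used as covariates if appropriate statistical assumptions are met". It names no variable and does not say what counts as a difference.

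Under Consent and Randomization, "a stratified random sampling procedure will be used, based on self-reported diabetic diagnosis", with a separate block schedule for diabetics and non-diabetics. The reason given there is that the definition of control differs between the two groups. The Primary outcome measure section confirms this: "BP control is defined as at or below 140/90 for non-diabetics and at or below 130/80 for diabetics".

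The primary outcome takes two forms: "Both the difference in the actual BP readings and the proportion of persons in each group achieving BP control at 180 days".

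- **Control (binary).** "Percentages will be compared using the arc sine transformation", at each time point, with no stratum or covariate named. Logistic regression for BP control appears only as an exploratory analysis, after the secondary hypotheses.
- **Continuous BP.** A mixed model is used, in which "the major effect of interest will be the linear group x time interaction". Diabetes is not named as a term.

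For patient activation, a secondary outcome, the article does fix a covariate in advance: "Analysis of covariance using the baseline activation score as covariate will be conducted".

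**The concern.** The rule selects on the wrong property. A covariate earns its place in a randomised comparison by predicting the outcome. Imbalance between arms is chance and is unrelated to prognostic value. Because the article sets no criterion for a difference, the final model can be settled only after the arms have been compared.

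The rule also works against the design. Diabetes was considered important enough to stratify on, and it decides which threshold a participant must meet. Blocking within strata keeps it balanced, so a search for differences will seldom pick it up. The binary comparison then treats each arm as one homogeneous group, and its variance includes between-stratum variation that the randomisation has already removed from the difference between arms. What is at stake is some precision on the main endpoint, and an open choice of model where a fixed one would cost nothing.

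**Working it through.** **1. The plan's own figure.** With 50 per group, d = 6/12 = .5 and one-sided alpha .05, power = Φ(.5 × √(50/2) − 1.645) = Φ(2.5 − 1.645) = .804. The binary case with h = .5 has the same formula and gives .804. The stated .80 reproduces. It was computed without adjustment.

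**2. Variance of the binary comparison with and without the stratum.** Let d be the proportion diabetic, a the control rate in diabetics and b the rate in non-diabetics. None of these is in the article, so I assume d = 25-40%, a = 20-30%, b = 50-60%.

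- Overall rate: p = d·a + (1 − d)·b
- Variance per person used by an unstratified comparison: M = p(1 − p). To first order the arc sine statistic corresponds to this variance on the proportion scale.
- Variance that remains when the arms are balanced on diabetes: W = d·a(1 − a) + (1 − d)·b(1 − b)
- Share of M that should not be there: R = 1 − W/M
- True size of a nominal one-sided .05 test: 1 − Φ(1.645 × √(M/W))

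| d | a | b | M | W | R | True size |
|---|---|---|---|---|---|---|
| .25 | .30 | .50 | .2475 | .2400 | 3.0% | .047 |
| .40 | .30 | .50 | .2436 | .2340 | 3.9% | .047 |
| .25 | .20 | .50 | .2444 | .2275 | 6.9% | .044 |
| .30 | .20 | .60 | .2496 | .2160 | 13.5% | .039 |
| .40 | .20 | .60 | .2464 | .2080 | 15.6% | .037 |

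The first and last rows are the extremes of the grid. R is expressed as a share of the unstratified variance. With a smaller gap between strata (d = .30, a = .40, b = .50), M = .2491, W = .2470, R = 0.8% and the size is .049, so the effect nearly vanishes.

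**3. What this means for power.** Keep h = .5 and 50 per group, and suppose R carries over to the alternative (an approximation). Unstratified power is Φ((2.5 − 1.645)/√(1 − R)); stratified power is Φ(2.5/√(1 − R) − 1.645).

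- R = 3.0%: .807 against .814.
- R = 15.6%: .824 against .859.

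The loss is about 1 to 4 percentage points, and in neither case does power fall below the stated .80.

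**4. What selection by imbalance recovers.** A simulation compared continuous BP at one follow-up time (6,000 runs, 50 per arm). It assumed a correlation of .5 between baseline and follow-up BP, 40% diabetic and balanced, diabetes correlated .2 with outcome, and eight further covariates of which five were weakly prognostic. The article gives no test for a difference, so p < .05 stood in for one.

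| Analysis | Power for 6 mmHg | SD of estimate (mmHg) | One-sided size |
|---|---|---|---|
| Unadjusted | .804 | 2.35 | .049 |
| Covariates chosen by baseline test | .814 | 2.25 | .040 |
| Baseline BP and diabetes fixed in advance | .901 | 2.03 | .050 |

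Imbalance selection recovers little of the available precision. This is not the article's mixed model, so the .901 is not a gain to expect there.

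**5. The mixed model.** The Study design and aims section says: "Study outcomes are assessed at baseline, 30, 90, and 180 days post ED discharge". Baseline BP therefore probably enters as the first time point. With compound symmetry and a linear effect reaching 6 mmHg at day 180, the slope contrast has power .738, .854 and .967 at correlations of .3, .5 and .7. Analysis of covariance on baseline gives .835, .893 and .968. A diabetes effect that is constant over time largely cancels from a contrast of within-person slopes.

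**The case against.** The strongest reply is that a condensed article may leave the list of model terms to a full protocol or SAP that is not shown. That holds for a missing term, but the point here is a selection rule that the article states. An SAP that follows it inherits the fault.

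It can also be said that blocking may be meant to enter the analysis, since the power paragraph mentions blocking and possible covariate adjustment as sources of extra power. The percentages paragraph also ends with general linear models across the assessment periods, which could carry covariates. Neither passage names a term, and the arc sine comparison remains as described.

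Four stronger readings might be inferred, and the article does not support them.

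- **The rule inflates type I error.** Applied mechanically it does not: the simulated size was .040. Taking the most favourable of 13 candidate models gave .104, but the article does not propose that. It only leaves the criterion open.
- **Spurious covariates are likely.** Screening ten independent variables at .05 would flag at least one with probability 1 − .95^10 = .40. The article states neither such a screen nor a list of ten.
- **Standard errors are too large in every primary analysis.** This concerns the binary comparison. It does not carry over to the group-by-time contrast.
- **Baseline BP is ignored.** For continuous BP it is an assessment time and changes in readings are analysed, so it is probably used.

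**Conclusion.** The point holds in a limited form. The covariate rule is poor as written, because it selects on chance imbalance with no criterion, and it tends to pass over the stratum that defines the BP-control threshold. For control at 180 days, the unstratified arc sine comparison carries about 3-16% excess variance and has a true one-sided size of about .037-.047 at nominal .05. Both ranges rest on assumed diabetes prevalence and control rates and on normal approximations, and they shrink towards nothing if control rates differ little between the strata. The error is on the conservative side: some power is given up and no false positives are added. The stated sample size and power stand. For continuous BP, little is lost by leaving diabetes out. The change is worth making because both variables are already collected, but it does not threaten the trial's validity.

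**What to change.** 1. Delete the sentence that takes covariates from baseline differences, and show baseline characteristics by arm descriptively.
2. For BP control at 180 days, replace the unstratified arc sine test with a Mantel-Haenszel comparison stratified by diabetes, or a logistic model with arm, diabetes stratum and baseline systolic BP as fixed terms. State which one is primary.
3. For continuous BP, keep the mixed model with group by time. Use baseline BP either as the first time point or as a covariate, not both. Include the diabetes stratum as a prespecified term, expecting little gain in precision. A model with only arm, stratum and baseline cannot simply replace the mixed model, because it has no time terms.
4. List any further prognostic covariates in advance.

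The cost is analysis wording only. Diabetes status is recorded for randomisation and BP is measured at baseline, so no new data are needed and the sample size is unaffected.

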### Study procedures

Once randomized, participants will complete their baseline assessments at the ED. Participants randomized into the intervention arm will be shown how to use the kiosk to answer questions and will complete the first health education module before leaving the ED.

To control for medication effects on blood pressure readings, all participants, regardless of study arm, will be prescribed a similar, evidence-based antihypertensive regimen [38], according to the algorithm illustrated in Fig. 3. Additionally all participants will receive an initial seven day medication supply at the conclusion of their ED visit. Participants on existing antihypertensive medication will have their medication adjusted to be in keeping with the study protocol. BP medication titration and side effect monitoring will occur at 7, 30, and 90 day post enrollment. All participants will receive primary care referrals as appropriate.

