### Intervention

An evidence-based patient education hypertension curriculum, developed by American TeleCare, Inc., will be provided through a portable touch screen kiosk (Aviva® 200: InLife™ XP Patient Monitor/LifeView™ Video Patient Station). The series of four modules are designed to provide patient education about BP control and to help build lifestyle decision-making skills. The hypertension curriculum, which was used in the investigator feasibility study, was developed in 2006 and revised in 2011. For the present study, the first kiosk session will be completed in the ED. A second kiosk located in the research facility will be used for three subsequent sessions to be completed at the 7, 30, and 90 day visits.

Research staff will show participants how to use the kiosk and will remain close by to answer questions that may arise. If desired, the kiosk can be set to read the material aloud and participants can control the pacing of the material by touching the screen when they are ready for the next item. Once the session is completed the kiosk will send the encrypted information to a secure place on the ATI server for storage and review by the research team.

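### Continuous blood pressure has its endpoint at 180 days but is tested by a linear slope difference, which understates a between-arm gap that opens early and then holds or fades

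*Protocol article*

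**What the plan says.** Under Primary outcome measure, the article uses "Both the difference in the actual BP readings and the proportion of persons in each group achieving BP control at 180 days" to judge the outcome. The natural reading is that the continuous reading and the proportion controlled share the 180-day time point. The abstract also places its endpoint, achieving control, at 180 days.

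Study design and aims fixes the visits: "Study outcomes are assessed at baseline, 30, 90, and 180 days post ED discharge".

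Under Statistical analysis, a mixed model is fitted to the continuous readings, and "for the continuous blood pressure measures, the major effect of interest will be the linear group x time interaction". The premise is "We assume that decreases in blood pressure over the time periods will be roughly linear, although a quadratic time effect may also occur". Power of .80 with 50 per group is given for a 6 mmHg systolic difference, SD 12 and one-sided alpha .05. The article adds: "This is a somewhat conservative estimate which does not take into account repeated measures, blocking, or possible covariate adjustments", and says that these features would tend to raise power.

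On timing, Study procedures states for drugs that "all participants will receive an initial seven day medication supply at the conclusion of their ED visit" and that "BP medication titration and side effect monitoring will occur at 7, 30, and 90 day post enrollment". Under Intervention, the first kiosk session takes place in the ED, and a second kiosk "will be used for three subsequent sessions to be completed at the 7, 30, and 90 day visits".

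**The concern.** The difference at day 180 and the difference in straight-line slopes agree only when the gap between arms grows in proportion to the time score. If it does not, the slope test answers another question from the one set under Primary outcome measure. A benefit that appears by day 30 and persists is partly counted against the kiosk arm, because early visits pull the fitted slope difference down.

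Two things are at stake. The trial could underestimate, or fail to detect, a difference that is present at its own endpoint. And the stated power belongs to a simple two-group comparison, not to the test named as the major effect, so the claim that it is conservative needs checking for that test.

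**Working it through.** **Inputs from the article.** SD 12 mmHg, target 6 mmHg, one-sided alpha .05, 50 per arm, visits at days 0/30/90/180.

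**Assumptions not in the article.** Within-person correlation r of .3 to .5, equal for all pairs of visits; complete data; illustrative gap shapes.

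**1. The plan's own figure.** SE = 12 x sqrt(2/50) = 2.40. 6/2.40 = 2.50. Power = Phi(2.50 - 1.645) = .804. The stated .80 reproduces, as a simple comparison of two means.

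**2. Weights in the slope.** Mean visit time is (0 + 30 + 90 + 180)/4 = 75 days. The weights are -75, -45, +15 and +105, with sum of squares 18,900. A 6 mmHg advantage at day 30 alone moves the fitted 180-day gap by 180 x (-45 x 6)/18,900 = -2.57 mmHg. With time scored by visit the weights are -1.5, -0.5, +0.5 and +1.5 (sum of squares 5), so the day-30 weight is still negative.

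**3. Formulas.**
- Fitted end gap = span x sum(weight x gap)/SS, with span 180 days or 3 visit steps.
- Its SE = span x 12 x sqrt((1 - r)/SS) x sqrt(2/50). In days this is 3.142 x sqrt(1 - r), or 2.63 at r = .3 and 2.22 at r = .5. By visit it is 3.220 x sqrt(1 - r), or 2.69 and 2.28.
- Baseline-adjusted day-180 contrast: SE = 2.40 x sqrt(1 - r^2), or 2.29 and 2.08.
- Power = Phi(gap/SE - 1.645).

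**4. Worked case: 6 mmHg from day 30, held.** Sum = 6 x (-45 + 15 + 105) = 450. Fitted gap = 180 x 450/18,900 = 4.29. 4.29/2.63 = 1.63, power .49; 4.29/2.22 = 1.93, power .61. The day-180 contrast gives 6/2.29 = 2.62, power .84, and 6/2.08 = 2.89, power .89.

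**5. Other shapes (power at r = .3 to .5).**

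| Gap at days 0/30/90/180 | Slope in days: fitted, power | Slope by visit: fitted, power | Day-180 contrast: power |
|---|---|---|---|
| 0/1/3/6, linear in days | 6.0, .74-.85 | 6.0, .72-.84 | .84-.89 |
| 0/0/3/6, late | 6.4, .79-.89 | 6.3, .76-.87 | .84-.89 |
| 0/3/4.5/6, builds with modules | 5.4, .65-.78 | 5.85, .70-.82 | .84-.89 |
| 0/3/6/6, full by day 90 | 5.6, .68-.81 | 6.3, .76-.87 | .84-.89 |
| 0/6/6/6, held | 4.3, .49-.61 | 5.4, .64-.77 | .84-.89 |
| 0/6/5/4, narrowing | 2.1, .20-.25 | 3.3, .34-.42 | .54-.61 |
| 0/6/4/2, fading | 0.0, .05 | 1.2, .12-.13 | .22-.25 |

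**6. Is the power statement conservative for the slope?** Power of .80 needs a gap of 1.645 + .842 = 2.487 SEs, so SE = 6/2.487 = 2.413. For a gap linear in days, sqrt(1 - r) = 2.413/3.142 = .768, so r = .41. Below that, slope power is under .80 even with the assumed shape. The day-180 contrast has SE of at most 2.40 at any r, so its power is never below .804.

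**7. Sensitivity.**
- At r = .7 the held gap reaches .80 in days, and the linear gap has .97 under both the slope and the day-180 contrast.
- With all 100 per arm retained, the held gap gives .75 to .86 in days.
- A quadratic time term common to both arms leaves the interaction unchanged in complete data.
- Handling of baseline matters. If the arms are constrained to be equal at baseline, r = .5 gives a held gap fitted as 5.5 mmHg with power .87. If baseline is a covariate and only days 30, 90 and 180 enter the slope, a held gap gives exactly zero.

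**The case against.** The strongest reply is that nothing in the article points to a gap that is complete by day 30. One module is given at each of baseline, day 7, day 30 and day 90, and the Background expects benefit from several brief sessions and repeated self-monitoring. That fits a gap that accumulates, for which the fitted loss is small (5.4 of 6 mmHg in days, 5.85 by visit). This stands: serious loss needs a gap that is complete early, or one that fades.

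A reader might infer from drugs starting at discharge, and titration ending at day 90, that the linear premise is already refuted. The document does not support that. The regimen and titration schedule are common to both arms, and a shared curved fall does not bias the interaction in complete data. Drug timing is no evidence about the gap between arms.

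A reader might also take the fading case (6, 4, then 2 mmHg, interaction exactly zero in days) as the main harm. It is a weak argument for change, because the day-180 contrast would have power of only .22 to .25 for it.

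The time score is not fixed in the article, and scoring by visit shrinks the loss. Correlation above about .41 makes the power sentence true for a gap linear in days. The proportions controlled are compared at each time point and are untouched. All of this stands and limits the size of the point. It does not remove the mismatch between a 180-day outcome and a slope test. Mentioning a possible quadratic effect does not help either, since the linear term stays the effect of main interest.

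**Conclusion.** The point holds as a worthwhile, inexpensive improvement, not as a demonstrated error. The slope named as the major effect is not the 180-day difference named as the outcome and used for power, and it weights a day-30 advantage negatively. For a 6 mmHg gap held from day 30, the fitted gap is 4.3 mmHg in days or 5.4 by visit, and power falls to .49-.61 or .64-.77, against .84-.89 for the baseline-adjusted day-180 contrast. The shortfall in the fitted gap is small if the gap builds with the modules and absent if it widens linearly or late. The description of the power as conservative is not assured for the slope, since it needs r of about .41 even for a gap linear in days; it is true of the day-180 contrast.

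These figures rest on an assumed r of .3 to .5, equal correlation between visits, complete data on 50 per arm, and illustrative shapes. No claim is made about which shape will occur. The analysis of proportions is not affected.

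**What to change.** In Statistical analysis, keep the mixed model but enter time as categories (30, 90 and 180 days) with adjustment for baseline blood pressure. Name the between-arm difference at day 180 as the primary contrast for the continuous readings. Keep the linear group x time term as a secondary description, drop reliance on the linear premise, and attach the power statement to the day-180 contrast. The article already takes this approach for patient activation, which is compared at 180 days by analysis of covariance on baseline.

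The cost is two or three sentences; patients, drugs, visits and sample size are unchanged. Little is lost if the gap does widen linearly: at r = .3, .5 and .7 the day-180 contrast has power .84, .89 and .97, against .74, .85 and .97 for the slope in days. The downside is that the primary test no longer credits the earlier visits, so a benefit that fades by day 180 will still usually be missed.
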